## Abstract

**Background and hypothesis:**

Retatrutide is an agonist of the glucose-dependent insulinotropic polypeptide, glucagon-like peptide-1 and glucagon receptors that reduced weight and hemoglobin A_1c_ (HbA_1c_) in individuals with obesity and type 2 diabetes (T2D). Retatrutide may also address key chronic kidney disease (CKD)-related pathophysiological pathways. Mechanism-of-action studies are needed to understand its effects on kidney function.

**Methods:**

TRANSCEND-CKD is a double-blind, placebo-controlled, Phase 2b mechanistic study evaluating the efficacy of retatrutide in adults with overweight/obesity and CKD [estimated glomerular filtration rate (eGFR) 25–75 mL/min/1.73 m^2^], with and without T2D. Participants were randomized 1:1 to once-weekly retatrutide maximum tolerated dose up to 12 mg or matched placebo. The primary objective is to evaluate the effect of retatrutide versus placebo on change in measured glomerular filtration rate (mGFR) by iohexol clearance from baseline to Week 24. Additional objectives include changes in magnetic resonance imaging–assessed kidney hemodynamic and volumetric measurements, including perirenal and renal sinus fat.

**Results:**

Of 367 participants screened, 146 were randomized to study interventions. The mean age was 65.1 years [standard deviation (SD) 10.6], 45.2% were female and 69.9% were White. The mean weight was 101.1 kg (SD 20.6) and body mass index 35.7 kg/m^2^ (SD 6.1). Participants with T2D (37.7%) had a mean HbA_1c_ of 7.1% (SD 1.1%), while HbA_1c_ was 5.7% (SD 0.3%) in participants without T2D. The mean mGFR was 49.3 mL/min/1.73 m^2^ (SD 19.0), cystatin C–based eGFR was 49.6 mL/min/1.73 m^2^ (SD 13.2) and creatinine-based eGFR was 64.2 mL/min/1.73 m^2^ (SD 17.8). The median baseline urine albumin-to-creatinine ratio was 14.0 mg/g (interquartile range 6.0–69.0). A total of 21.8% of participants were treated with sodium-glucose cotransporter-2 inhibitors at baseline.

**Conclusions:**

TRANSCEND-CKD is designed to provide mechanistic insights on the effects of retatrutide on kidney function and structure, and to inform clinical findings in the ongoing cardio-kidney outcome trial TRIUMPH-Outcomes (NCT06383390).

**Clinical Trial Registration Number:**

NCT05936151

KEY LEARNING POINTS
**What was known:**
Retatrutide is an agonist of the glucose-dependent insulinotropic polypeptide, glucagon-like peptide-1 and glucagon receptors that reduced body weight in participants with obesity and type 2 diabetes (T2D) and may impact key chronic kidney disease (CKD)-related pathophysiological pathways.The mechanisms-of-action of retatrutide on kidney function and potential clinical impact are not yet fully understood.
**This study adds:**
This Phase 2b, 24-week study investigates the kidney-specific mechanisms-of-action of retatrutide in participants with overweight/obesity and CKD, with or without T2D.This study integrates gold standard measure of glomerular filtration rate by iohexol clearance, multiparametric kidney magnetic resonance imaging to assess kidney hemodynamics and structure, as well as renal and abdominal adipose tissue, and biomarkers of kidney tissue damage and injury.
**Potential impact:**
Findings from this study will help explain the effects of retatrutide on kidney function and structure already observed in completed trials and inform ongoing kidney outcomes studies.In addition, since retatrutide includes glucagon receptor agonism, the trial is expected to provide mechanistic insights into this pathway in the kidney, where glucagon signaling has been shown to serve an important physiological role.

## INTRODUCTION

Obesity precedes and often accelerates the onset of type 2 diabetes (T2D) and hypertension, both well-known risk factors for chronic kidney disease (CKD) development [1]. Obesity can also cause CKD in individuals without diabetes through mechanisms unrelated to hyperglycemia. In recent years, new therapies have become available for the management of CKD, including sodium-glucose cotransporter-2 inhibitors (SGLT2i) and a non-steroidal mineralocorticoid receptor antagonist. Despite these new therapies, the residual risk remains high and the prevalence of CKD continues to rise and is estimated to affect more than 800 million people globally [2]. Additional therapies to improve the pharmacological management of CKD are urgently needed.

The discovery of the gut hormones glucagon-like peptide-1 (GLP-1) and glucose-dependent insulinotropic polypeptide (GIP) has transformed the management of T2D [3]. In addition, these incretin receptor agonists (RAs) reduce obesity and associated cardiometabolic complications [3]. Specifically, GLP-1 RAs have consistently been shown to confer cardiovascular protection in individuals with T2D and/or obesity [4–6]. In addition, a GLP-1 RA, semaglutide, slowed the progression of CKD and reduced the risks of clinically meaningful kidney and cardiovascular outcomes in patients with T2D and CKD [7]. A dual GIP and GLP-1 RA, tirzepatide, has been approved for the treatment of T2D, obesity and obstructive sleep apnea. Secondary analyses from clinical trials have shown tirzepatide to reduce albuminuria in people with and without T2D compared with placebo or insulin-based treatments [8, 9]. In addition, tirzepatide slowed the decline in estimated glomerular filtration rate (eGFR) compared with insulin glargine in participants with T2D and high cardiovascular disease risk [10].

Emerging insights into the role of glucagon in metabolism and energy expenditure have motivated the development of specific agonists, such as retatrutide, that target the GIP, GLP-1 and glucagon receptors [11]. In experimental models, retatrutide increased energy expenditure and reduced calorie intake [12]. In two Phase 2 clinical trials in participants with T2D and in participants with overweight or obesity without T2D, retatrutide improved glycemic control and reduced body weight along with reductions in blood pressure, cholesterol and markers of inflammation [13, 14]. A dedicated kidney analysis from these two clinical trials focusing on changes in eGFR and albuminuria over time, reported an initial decrease in eGFR with retatrutide, followed by an eGFR increase to baseline values in patients with T2D and even exceeding baseline eGFR in participants with overweight or obesity and without T2D [15]. The eGFR increase at 24 weeks with retatrutide in those with obesity or overweight could reflect an increase in glomerular pressure, potentially leading to single nephron hyperfiltration and structural damage. In earlier studies in both rodents and humans, glucagon infusion was shown to increase GFR, likely by reducing pre-glomerular arteriolar resistance [16, 17]. However, such hemodynamic changes would typically increase albuminuria, which instead decreased significantly with retatrutide versus placebo or dulaglutide, particularly in those with more severe albuminuria [15]. It is also possible that a decrease in body surface area due to weight loss contributes to the increase in eGFR when indexed for 1.73 m^2^ body surface area [18]. The mechanisms contributing to the increase in eGFR are unclear. We hypothesize that retatrutide reduces peri-renal and intra-abdominal adipose tissue, thereby relieving glomerular compression and improving kidney hemodynamic function. It is also possible that reductions in body composition and fat mass during retatrutide treatment affect endogenous filtration markers such as creatinine or cystatin C without real effects on glomerular filtration. A dedicated mechanism-of-action trial on kidney function and structure is therefore critical to elucidate the mechanism of retatrutide on GFR and albuminuria and to interpret and contextualize the forthcoming clinical findings from the Phase 3 TRIUMPH-Outcomes trial (NCT06383390) investigating the effects of retatrutide on cardiovascular and kidney outcomes in participants with obesity, with estimated completion in 2029. We here describe the study design and baseline characteristics of the TRANSCEND-CKD randomized, placebo-controlled trial designed to characterize the mechanism of action of retatrutide on kidney function and structure.

## MATERIALS AND METHODS

### Study design and participants

This is a Phase 2b, double-blind, 24-week study (NCT05936151) conducted at 42 sites in Canada, Italy, Spain, the UK and USA. The study included a screening period, a treatment period and a safety follow-up period (Fig. 1). Participants were randomly assigned in a 1:1 ratio to once-weekly subcutaneous injection of retatrutide maximum tolerated dose up to 12 mg or matching placebo. Randomization was stratified by T2D status at baseline (with or without T2D), eGFR category (≥25 to <45, ≥45 to <60 and ≥60 to ≤75 mL/min/1.73 m^2^) based on cystatin C eGFR, and treatment with SGLT2i at baseline (yes or no). Retatrutide was initiated at 2 mg once weekly, and the dose was increased every 4 weeks until the randomization dose of 12 mg was achieved (Fig. 1). If the 12 mg dose was not well tolerated, the 4, 6 or 9 mg dose was allowed. All the participants received a lifestyle intervention that included regular individualized counselling sessions for a healthy diet delivered by a dietitian or qualified health care professional. An increased physical activity to at least 150 min/week was also encouraged.

**Figure 1: fig1:**
[figure not shown]
Study design of the Phase 2b renal mechanism-of-action study of retatrutide. QW, once weekly.

Eligible participants were adults with overweight or obesity [body mass index (BMI) ≥27 kg/m^2^] and established CKD at screening, with or without T2D, on stable treatment for at least 90 days before screening with an angiotensin-converting enzyme (ACE) inhibitor or angiotensin II receptor blockers (ARB) that was considered the maximal appropriate dose per local label and by the investigator for treatment of CKD or hypertension (Table 1). The use of SGLT2i was also allowed if stable for at least 90 days before screening.

**Table 1: tbl1:** Key inclusion and exclusion criteria of the Phase 2b renal mechanism-of-action study of retatrutide.

Inclusion criteria	Exclusion criteria
• 18 years of age or older at the time of signing the informed consent	• Self-reported change in body weight >5 kg (11 lbs) within 90 days before screening
• BMI ≥27 kg/m^2^• Eithero No T2D diagnosis with an HbA_1c_ <6.5% (<48 mmol/mol) Oro T2D diagnosis with an HbA_1c_ ≤9.5% (≤80.34 mmol/mol) and treated with diet and exercise only or with stable doses of up to three oral antihyperglycemic medications per local labeling, such as metformin, sulfonylurea, meglitinides, SGLT2i or thiazolidinediones, with or without basal insulin, for at least 90 days before screening• CKD diagnosis and eGFR ≥25 to ≤75 mL/min/1.73 m^2^, calculated using cystatin C–based CKD-EPI equation• On stable treatment, for at least 90 days before screening, with an ACE inhibitor or ARB that was considered the maximal appropriate dose per local label and by the investigator for treatment of CKD or hypertension. The use of SGLT2i was allowed in participants without T2D, in which case, the dose was stable for at least 90 days before screening^a^	• Used in 90 days before screening any of the following antihyperglycemic medications: DPP4 inhibitors, amylin analogs, GLP-1 RAs, GIP/GLP-1 RA and short-acting or rapid-acting insulins or U500 Insulin• Prior or planned surgical treatment for obesity• Type 1 diabetes• Acute or chronic hepatitis• History of malignant disease within 5 years before screening

^a^Participants who were intolerant to ACE inhibitors or ARBs were allowed to enter the study.

DPP4: Dipeptidyl Peptidase IV.

### Ethics

TRANSCEND-CKD is being conducted in accordance with ethical principles derived from the Declaration of Helsinki, the Council for International Organizations of Medical Sciences International Ethical Guidelines, the International Council for Harmonisation Good Clinical Practice Guidelines and all applicable laws and regulations. Before the study was initiated, the protocol, protocol amendments, informed consent and other forms were reviewed and approved by a local independent review board/ethics committee. All study participants provided written, informed consent before study-specific procedure commenced. All participants were informed that their participation in the study was voluntary, and they may withdraw their consent at any time.

### Objectives and endpoints

The primary objective of this study was to compare the effect of retatrutide versus placebo for the change in measured glomerular filtration rate (mGFR) by iohexol clearance from baseline to Week 24 (Table 2). Secondary objectives included comparing the effect of retatrutide versus placebo for the change in mGFR from baseline to Week 16 and comparing the effect of retatrutide versus placebo for the change in glomerular and tubular functional measurements, magnetic resonance imaging (MRI)-assessed kidney hemodynamic function and volumetric measurements and kidney injury and function, kidney oxygenation measured by kidney blood oxygenation level-dependent (BOLD) MRI, and body weight from baseline to Week 16 and from baseline to Week 24 (Table 2). Exploratory objectives included comparing the effect of retatrutide to placebo for the change from baseline to Week 16 and from baseline to Week 24 in kidney and abdominal adipose tissue, and renal diffusion, assessed using non-invasive, multimodal MRI techniques, and creatinine- and cystatin C–based eGFR. Adverse events and serious adverse events were included in the safety assessments.

**Table 2: tbl2:** Primary and secondary objectives and endpoints of the Phase 2b renal mechanism-of-action study of retatrutide.

Objectives	Endpoints
**Primary**	
To compare the effect of retatrutide vs placebo on mGFR from baseline to Week 24	Change in mGFR (mL/min/1.73 m^2^) using iohexol clearance
**Secondary**	
To compare the effect of retatrutide vs placebo on mGFR from baseline to Week 16	Change in mGFR (mL/min/1.73 m^2^) using iohexol clearance
To compare the effect of retatrutide vs placebo from baseline to Week 16 and baseline to Week 24 for	
• Glomerular and tubular functional measurements	• Change in:
	o UACR^a^
	o Creatinine-corrected FENa
	o Filtration fraction estimated from mGFR and MRI-assessed renal mean arterial flow, corrected by hematocrit
	o Markers of glomerular and tubular function including nephrin KIM-1, NAG, LFABP, clusterin and IL-18
• Renal hemodynamic measurements by MRI	• Change in:
	o Mean arterial flow
	o Renal artery resistive index
	o Renal blood flow velocity (PSV and EDV)
	o Global renal perfusion
• Renal volumetric measurements assessed by MRI	• Change in:
	o Total renal parenchyma volume
	o Renal cortex volume
• Renal injury and function by MRI	• Change in:
	o Renal cortex T_1_ (ms)
	o Renal medulla T_1_ (ms)
• Kidney oxygen availability measured by kidney BOLD MRI	• Change in:
	o Renal cortex R_2_*
	o Renal medulla R_2_*
• Body weight	• Percent change in body weight
To compare the effect of retatrutide vs placebo on glomerular and tubular functional measurements from baseline to Week 24	• Change in 24-h UAE (mg/24 h)
	• Change in 24-h urinary electrolytes (mg/24 h)

a Change in UACR will be analyzed in a subset of participants with baseline UACR ≥30 mg/g.

BOLD, blood oxygenation level-dependent; EDV, end-diastolic velocity; FENa, fractional urinary sodium excretion; IL, interleukin; KIM-1, kidney injury molecule 1; PSV, peak systolic velocity; R_2_*, the inverse of transverse relaxation time constant measured by MRI; T_1_, longitudinal relaxation time of tissue measured by MRI; UAE, urinary albumin excretion.

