#### Urinary albumin excretion

Spot urine samples will be collected at baseline, Weeks 4, 12, 16 and 24, and after a 4-week wash-out (Week 28) for assessment of urine albumin–creatinine ratio (UACR). Twenty-four-hour urine samples are also collected at baseline and Week 24 to determine 24-h albumin excretion rate.

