### Statistical considerations

#### Sample size determination

A sample size of 120 randomized participants, approximately 60 participants in each of the retatrutide and placebo arms, was calculated to provide at least 80% power to establish a significant difference in the change from baseline to Week 24 in mGFR between retatrutide and placebo. The calculation assumed a 15% dropout rate, a two-sided two-sample *t*-test with significance level of 0.05, a standard deviation (SD) of 8.1 and a mean change from baseline in mGFR of 4.56 mL/min/1.73 m^2^ at Week 24 in participants receiving retatrutide compared with placebo based on eGFR data from the Phase 2 studies [13–15].

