#### Statistical analyses

The main analysis includes participants who were randomly assigned a study intervention and took at least one dose of study intervention and used the efficacy estimand. The efficacy estimand is based on the hypothetical strategy to address intercurrent events [21]. In this hypothetical strategy, the primary clinical question of interest asks what the treatment difference is in mGFR change from baseline at 24 weeks between retatrutide and placebo in participants who meet the eligibility criteria if they would remain on their randomly assigned treatment for 24 weeks and would not initiate new SGLT2i, ACE inhibitor or ARB. In the efficacy estimand, a mixed model repeated measures analysis model will be used to analyze continuous measurements with multiple postbaseline measures with terms of treatment, visit, stratification factors, baseline measurement, treatment-by-visit interaction and baseline measurement-by-visit interaction. An analysis of covariance will be used to analyze continuous measurements with only one post-baseline assessment with terms of treatment, stratification factors and baseline measurement. The missing data will be imputed using non-missing data within the same treatment group at the same visit under the missing at random assumption. The estimated treatment difference between retatrutide and placebo will be presented along with the two-sided 95% confidence interval and *P*-value. No adjustments for multiplicity will be performed for primary and secondary objectives. Safety assessments used an estimand comparing the safety of retatrutide with that of placebo, irrespective of adherence to study intervention.

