Data are reported as means with SD, medians with interquartile range (IQR) or numbers with percentage (%).

BSA, body surface area; CVD, cardiovascular disease; DPP4, Dipeptidyl Peptidase IV; HDL, high-density lipoprotein; LDL, low-density lipoprotein.

The mean baseline iohexol mGFR was 49.3 mL/min/1.73 m^2^ (SD 19.0), the cystatin C–based eGFR was 49.6 mL/min/1.73 m^2^ (SD 13.2) and the creatinine-based eGFR was 64.2 mL/min/1.73 m^2^ (SD 17.8). The median baseline UACR was 14.0 mg/g (interquartile range 6.0–69.0), with 30.1% of participants having ≥30 mg/g at baseline.

A total of 35.9% of participants were receiving ACE inhibitors, and 58.5% were on ARB. Overall, 74.6% of participants were taking lipid-lowering medications, 21.8% were using SGLT2i, 25.4% metformin, 4.2% sulfonylurea and 4.2% basal insulin. Other baseline clinical characteristics are presented in Table 3.

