GFR estimation equations may be affected by significant weight loss, as changes in creatinine or cystatin C may reflect reduction in muscle or fat mass without actual changes in glomerular filtration. In a previous Phase 2 study in people with T2D, no correlations were observed between changes in creatinine- or cystatin C–derived eGFR and changes in body weight, suggesting that changes in body weight did not impact eGFR [15]. However, in adults with overweight or obesity, a change in body weight after 48 weeks of treatment with retatrutide at a dose of 12 mg once weekly correlated with an increase in creatinine-based eGFR [15]. This was not observed for cystatin C–based eGFR, suggesting that cystatin C–based eGFR is the preferred method to monitor eGFR during treatment with retatrutide. However, the prior studies did not measure GFR and included only a limited number of patients with CKD. Comparing changes in mGFR with eGFR by creatinine or cystatin C during retatrutide treatment in the TRANSCEND-CKD will inform the optimal method to monitor changes in kidney function over time. To characterize acute changes in mGFR upon initiation of retatrutide, an additional GFR measurement at 4 weeks was considered during the design of the study, but decided not to include due to feasibility and operational concerns. The collection of 24-h urine samples in TRANSCEND-CKD also allows comparison of 24-h creatinine clearance with other GFR assessment. Changes in lean body weight may also affect 24-h creatinine clearance and impact effects of retatrutide on UACR, as previously noted [40]. The effects of retatrutide on 24-h urinary albumin excretion will be assessed in the current study to determine whether changes in urinary creatinine excretion underestimate effects on UACR.

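### UACR is limited to participants with baseline UACR ≥30 mg/g and 24-h UAE is not, so comparing the two effects as specified mixes case mix with any creatinine effect

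*Protocol article*

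**What the plan says.** - **UACR.** Table 2 lists change in UACR as a secondary endpoint at Weeks 16 and 24. Footnote a adds: "Change in UACR will be analyzed in a subset of participants with baseline UACR ≥30 mg/g". The baseline results describe the cohort "with 30.1% of participants having ≥30 mg/g at baseline", and Table 3 gives 44 participants at or above that threshold and 102 below it.
- **24-h UAE.** Change in UAE is a separate secondary endpoint, at Week 24 only. It carries no footnote. The general rule under Statistical analyses therefore applies: "The main analysis includes participants who were randomly assigned a study intervention and took at least one dose of study intervention".
- **Collection.** The section on urinary albumin excretion sets no albuminuria threshold for either sample: "Spot urine samples will be collected at baseline, Weeks 4, 12, 16 and 24", and "Twenty-four-hour urine samples are also collected at baseline and Week 24 to determine 24-h albumin excretion rate".
- **Use.** The Discussion notes that changes in lean body weight may affect the UACR result. It says the effect on 24-h UAE will be assessed "to determine whether changes in urinary creatinine excretion underestimate effects on UACR".
- **Prior evidence.** The Introduction reports that in the earlier Phase 2 analysis the fall in albuminuria was most evident in participants with more severe albuminuria.

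**The concern.** UAE is meant to serve as the reference that is free of urinary creatinine. If UACR falls less than UAE, the natural reading is that creatinine excretion also fell and that UACR understates the benefit. That reading requires both effects to be estimated in the same participants.

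As the endpoints are written, the UACR effect comes from the albuminuric 30% and the UAE effect from everyone. Baseline albuminuria defines the subset, and by the article's own account it also modifies the effect. A gap between the two estimates then has two possible sources, creatinine excretion and case mix, and the two results alone cannot separate them. At stake is the interpretation of one mechanistic comparison between secondary endpoints.

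**Working it through.** **1. Counts (Table 3).** 44/146 = 30.1% and 102/146 = 69.9%, with 44 + 102 = 146. These reproduce the printed percentages. As written, about 70% of the randomised participants can contribute to the UAE estimate but not to the UACR estimate.

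**2. The two endpoints side by side.**

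| | UACR | 24-h UAE |
|---|---|---|
| Analysed in | baseline UACR ≥30 mg/g | all randomised and dosed (default) |
| Randomised participants | at most 44 | at most 146 |
| Endpoint visits | Weeks 16 and 24 | Week 24 |
| Sample collected in | no albuminuria restriction | no albuminuria restriction |

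**3. Can case mix alone create a gap?** The effects below are assumptions, because the article gives none. Suppose that effects are ratios to placebo on the log scale, that the 44:102 split is the same in both arms, and that treatment does not change creatinine excretion. Within any group the UACR and UAE effects are then equal. With reduction r1 at or above 30 mg/g and r2 below it:

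log(UAE ratio, all) = (44/146) × log(1 − r1) + (102/146) × log(1 − r2)

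For r1 = 30% and r2 = 10%: 0.301 × (−0.357) + 0.699 × (−0.105) = −0.181. The ratio is 0.834, a reduction of 16.6%.

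| r2 (below 30 mg/g) | UAE reduction, all | UACR reduction, subset | UACR ratio ÷ UAE ratio |
|---|---|---|---|
| 0% | 10.2% | 30% | 0.779 |
| 10% | 16.6% | 30% | 0.839 |
| 20% | 23.2% | 30% | 0.911 |
| 30% | 30.0% | 30% | 1.000 |

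Without any creatinine effect, the two estimates agree only when the effect is the same on both sides of the threshold.

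**4. Can case mix hide a real creatinine effect?** If treatment lowers creatinine excretion by a fraction c relative to placebo, the subset UACR ratio becomes 0.70/(1 − c). It equals the all-participant UAE ratio when 1 − c is the last column above, so c = 1 − 0.779 = 22.1%, 1 − 0.839 = 16.1% or 1 − 0.911 = 8.9%. In those cases UACR does understate the albumin reduction in the subset, yet the two published estimates would agree. This is the direction of error that the Discussion wants to detect.

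**5. Price of matching in the subset.** With equal SD, the standard error for UAE in 44 rather than 146 participants is larger by √(146/44) = 1.82. If the 15% dropout from the sample-size section applied, 44 × 0.85 gives about 37 evaluable participants.

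**The case against.** **The article does not state the flawed comparison.** The Discussion sentence names no population, model or contrast. The full protocol or SAP, neither of which is shown, may pair the analyses. This stands, and it limits the point to the endpoints as Table 2 and the general population rule define them. It does not remove the point: the article itself restricts one of two linked endpoints and leaves the other unrestricted.

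**The restriction is a reasonable choice.** Median baseline UACR is 14 mg/g and 69.9% of participants are below 30 mg/g, so most have little albuminuria to reduce. This stands too, and the subset analysis need not be demoted. UACR category was not a stratification factor, but the subset is defined at baseline and treatment remains randomised within it.

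**Creatinine excretion can be examined directly.** The Discussion plans 24-h creatinine clearance from the same collections, so creatinine excretion can be compared by arm. This is true and useful, but the article names the UAE effect as its instrument.

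A reader might draw three stronger conclusions that the document does not support:

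- *That UACR and UAE are measured in different people.* The 44 are part of the UAE population; the groups are nested.
- *That the question cannot be answered.* Both samples are collected without restriction, so a matched comparison needs no new data.
- *That the restriction should go because it costs power.* At an assumed log SD of 0.7 (the article gives none), power for a 30% reduction is about 33% with 19 per arm and 80% with 62 per arm. That contrast assumes the same 30% reduction below 30 mg/g, which conflicts with the Introduction. With 0%, 10% or 20% there, all-participant power is about 14%, 30% or 55%. The article claims no power for UACR, and the point needs none.

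**Conclusion.** The point holds as a mismatch between two linked secondary endpoints. UACR covers at most 44 of 146 randomised participants, UAE defaults to all who were dosed, and the Discussion interprets one against the other. Under the assumed effects above, case mix alone puts all-participant UAE at about 10% to 23% against 30% for UACR, or masks a fall in creatinine excretion of about 9% to 22%.

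These sizes rest on assumed effects, a log-scale analysis and an equal split of the subset between arms. The direction rests on the Introduction's statement that the effect is larger in more severe albuminuria; if the effect were the same throughout, the problem would vanish. The count of 44 is of randomised participants, so the analysed number may be smaller. The medication percentages in Table 3, for example, fit a denominator of 142 (134/142 = 94.4%). The primary mGFR endpoint and its sample size are not affected.

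**What to change.** - Keep the UACR analysis in participants with baseline UACR ≥30 mg/g as planned.
- Add change in 24-h UAE in that same subset, and change in UACR in all dosed participants as a supportive analysis. Express both measures as log-scale change from baseline to Week 24, the only post-baseline visit for UAE.
- State that the comparison described in the Discussion uses participants with both measures, in the subset and then in all dosed participants. Do not set the subset UACR estimate against the all-participant UAE estimate.

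If the full protocol or SAP already does this, one clarifying sentence in the article is enough. Otherwise the cost is additional tables, with no new visits or samples. The downside is lower precision for UAE in the subset of about 44. The all-participant UACR effect may also be smaller than the subset effect, which is a reason to keep it supportive.
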